## Abstract

**Background:**

In principle, risk-stratification as a routine part of the NHS Breast Screening Programme (NHSBSP) should produce a better balance of benefits and harms. The main benefit is the offer of NICE-approved more frequent screening and/ or chemoprevention for women who are at increased risk, but are unaware of this. We have developed BC-Predict, to be offered to women when invited to NHSBSP which collects information on risk factors (self-reported information on family history and hormone-related factors via questionnaire; mammographic density; and in a sub-sample, Single Nucleotide Polymorphisms). BC-Predict produces risk feedback letters, inviting women at high risk (≥8% 10-year) or moderate risk (≥5 to < 8% 10-year) to have discussion of prevention and early detection options at Family History, Risk and Prevention Clinics. Despite the promise of systems such as BC-Predict, there are still too many uncertainties for a fully-powered definitive trial to be appropriate or ethical. The present research aims to identify these key uncertainties regarding the feasibility of integrating BC-Predict into the NHSBSP. Key objectives of the present research are to quantify important potential benefits and harms, and identify key drivers of the relative cost-effectiveness of embedding BC-Predict into NHSBSP.

**Methods:**

A non-randomised fully counterbalanced study design will be used, to include approximately equal numbers of women offered NHSBSP (*n* = 18,700) and BC-Predict (*n* = 18,700) from selected screening sites (*n* = 7). In the initial 8-month time period, women eligible for NHSBSP will be offered BC-Predict in four screening sites. Three screening sites will offer women usual NHSBSP. In the following 8-months the study sites offering usual NHSBSP switch to BC-Predict and vice versa. Key potential benefits including uptake of risk consultations, chemoprevention and additional screening will be obtained for both groups. Key potential harms such as increased anxiety will be obtained via self-report questionnaires, with embedded qualitative process analysis. A decision-analytic model-based cost-effectiveness analysis will identify the key uncertainties underpinning the relative cost-effectiveness of embedding BC-Predict into NHSBSP.

**Discussion:**

We will assess the feasibility of integrating BC-Predict into the NHSBSP, and identify the main uncertainties for a definitive evaluation of the clinical and cost-effectiveness of BC-Predict.

**Trial registration:**

Retrospectively registered with clinicaltrials.gov (NCT04359420).

## Background

Breast cancer is the most common cancer in the UK and a leading cause of death in women [1]. Each year, approximately 55,000 women are diagnosed with breast cancer, of whom approximately 11,400 will die from the disease [1]. Although deaths from breast cancer have been decreasing in many Western countries, the incidence of breast cancer is continuing to increase [2–4]. To identify breast cancer at an earlier and more treatable stage, nearly two million women are screened in the National Health Service Breast Screening Programme (NHSBSP) in England every year [5]. The NHSBSP currently invites women aged 50 to70 years (though some breast screening units are trialling screening from ages 47 to 73 years) for three-yearly mammograms. The NHSBSP also undertakes screening of very high-risk women with high-penetrance mutations in genes such as *BRCA1, BRCA2* and *TP53.* These women are offered annual Magnetic Resonance Imaging screening between ages 30 to 50 years and annual mammography between 40 to 70 years.

In 2013, the National Institute for Health and Care Excellence (NICE) recommended that women at high risk of breast cancer who are not high penetrance gene carriers (lifetime risk ≥30%, 10-year risk ≥8%), should be offered annual breast screening between the ages of 40 to 59 years; and those at moderate risk (lifetime risk 17–29%, 10-year risk 3–7.9% aged 40 years), should be offered annual mammography from 40 to 49 years [6], but considered for annual screening aged 50 to 59 years. NICE guidance also recommends that women at high risk of breast cancer are offered chemoprevention with tamoxifen, anastrozole or raloxifene (considered in moderate risk) and advice on weight control and physical activity [6]. So far, it is estimated that only about 1 in 6 women who are at high-risk as defined by NICE (≥8% ten-year risk of breast cancer) have been actively identified by attending Family History, Risk and Prevention (FHRP) Clinics [7, 8].

Risk stratification in the NHSBSP could identify many of the 5 in 6 women who are at high-risk but are not aware of this, as well as a larger number of women at moderate risk. It is possible to accurately estimate a woman’s individual risk of developing breast cancer through information on breast density derived from mammography and self-report questions assessing family history and factors affecting hormone levels, e.g. using the Tyrer-Cuzick algorithm [9]. A previous study (PROCAS) provided 10-year risk estimates to over 54,000 women in the NHSBSP in Manchester, England [10]. This study was the first time that personalised breast cancer risk estimates were calculated for large numbers of women from the general breast screening population. The PROCAS study found that at least 3% of women are high risk (≥8% 10-year risk) when all risk factors including mammographic density are assessed and a further 10% are at moderate risk (5–7.9% 10-year risk) [7, 8]. Given that only 0.5% of the population have identified themselves as high risk, this means that there are approximately an additional 450,000 women in England (aged 30 to 70 years) at high risk that NICE guidance indicates should be offered chemoprevention and annual mammography.

The introduction of risk stratification in the NHSBSP could allow the potential benefits of more frequent screening and/ or chemoprevention to be realised on a population basis, and potentially allow women at lower risk to have less frequent screening recommended. In principle, a risk-stratified NHSBSP should result in a better balance of benefits, harms and NHS costs and there is some emerging early evidence to support this premise [11]. The benefits might be fewer breast cancers due to chemoprevention, and reduced breast cancer mortality arising from NHSBSP detecting more breast cancers at an earlier and more treatable stage. There might also be grounds for reducing screening for women at lower risk, who would be less likely to develop high grade tumours [12]. Reducing screening in women at lower risk would produce fewer harms of screening in this group, such as fewer false positive test results in lower risk women [13].

The consequences of introducing risk stratified screening in the NHSBSP are unclear. In the PROCAS study, communication of risk estimates happened 3 to 5 years after women provided their questionnaire data and consent [10], so that study provides limited information about the consequences of receiving risk estimates: the main purpose of that study was to validate risk prediction algorithms rather than as a new screening service model [8]. It is likely that, if aware of their risks, a sizeable proportion of women at high/moderate-risk would opt for chemoprevention with anastrozole/raloxifene/tamoxifen [7, 8, 10, 14, 15], as well as extra mammography in high-risk women [8]. The overall net effect of chemoprevention and additional screening is likely to be beneficial from a reduction in breast cancer incidence and mortality. By contrast, there are also several possible harms that could be brought about by the receipt of risk estimates. Communicating personal risk information to women could induce undue anxiety and worry. Although the best available evidence suggests that this is unlikely, this evidence has limitations such as a long time-lag between women agreeing to risk assessment and receiving risk results [16].

In addition, the mere offer of risk stratified screening may have potential adverse effects. It is possible that by offering risk stratified screening as part of the NHSBSP, women are put off from attending screening and thereby receiving its benefits. Evidence from PROCAS [10] suggests this is unlikely. Furthermore, as with all screening programmes within the NHS it is important that patients are provided with the necessary information in order to possess the knowledge to make an informed personal decision about whether to attend screening, and any treatment options that follow from screening [17]. There is currently no clear evidence to indicate whether risk-stratified screening could result in more informed decisions or not [18].

A final important group of possible drawbacks of implementing risk stratification are the potential costs, both personal and financial, to implementing the communication of risk information on such a scale, including increased NHS staff workload and additional healthcare resources. Evidence is therefore required about the key drivers of the relative cost-effectiveness of communicating breast cancer risk estimates compared with current NHSBSP practice, understanding the key uncertainties in the current evidence base and potential value of future research [19]. Overall, it is imperative in order to highlight whether risk stratified screening will induce harms and if so, how they can be mitigated so as not to outweigh benefits, and allow more effective use of healthcare resources.

We have developed an automated system (BC-Predict) for offering an assessment of breast cancer risk to women when they receive their NHSBSP invitation, and generating letters to feedback this risk to women and relevant healthcare professionals. A development phase involved working with healthcare professionals that ensured that the care pathways were workable, and that informatics procedures functioned as intended. The patient information materials were co-produced with women who would be eligible for BC-Predict to promote good understanding and informed choices, and also minimise harms such as unnecessary worry.

In BC-Predict, risk estimation can be offered in real-time to women invited for breast screening via an online web system to allow consent and self-report measures to be provided. Risk assessment is based on self-report questions and breast density estimates automatically derived from mammography, and can also incorporate information from currently known breast cancer Single Nucleotide Polymorphisms (SNPs), derived from DNA contained in saliva samples. Women who receive a clear mammogram result are then sent a letter providing their 10-year breast cancer risk within 6 to 8 weeks after their mammogram. Thus all women will know their risks. Those women at moderate (> 5% but < 8% 10-year risk) or high (≥8% 10-year) risk are encouraged to attend a consultation at a FHRP Clinic, to discuss the offer of more frequent screening and chemoprevention.

Although developmental work has shown BC-Predict to function as intended, it would not be appropriate to implement a system such as BC-Predict outside of a research setting, given the uncertainties around potential benefits, possible harms and cost effectiveness [20]. It would not even be proportionate or ethical to conduct the required large-scale definitive evaluation of clinical and cost-effectiveness, as this which would require the participation of hundreds of thousands of women to have sufficient power to detect its effect on breast cancer incidence and stage. Therefore, in line with the MRC Framework for Developing and Evaluating Complex Interventions [21], the present research has the goal of identifying and resolving key uncertainties regarding the feasibility of integrating BC-Predict into the NHSBSP and assessing the feasibility of a definitive study to assess whether the intervention translates into measurable effects on breast cancer incidence and stage, and is a cost-effective use of NHS resources. The present research will therefore quantify key drivers of the relative cost-effectiveness of communicating breast cancer risk estimates compared with current NHSBSP practice, understanding the key uncertainties in the current evidence base and potential value of future research.

A particular concern during the development phase was that that women from low socioeconomic and minority ethnic backgrounds are less likely to attend for screening [22–24]. Commonly cited reasons include language barriers, cultural incongruences and lack of understanding and knowledge about screening [22, 25, 26]. It is not presently known whether the introduction of risk-stratified screening would exacerbate these issues further or lead to increased non-attendance. In developing BC-Predict, interviews with a cohort of British-Pakistani women from low socioeconomic backgrounds found that views toward risk-stratified screening are favourable. However, as with the present screening programme language barriers could still prevent access and reduce women’s ability to make informed decisions [27]. Given this, in the present study we will assess whether women from low socioeconomic status backgrounds are less likely to take up the offer of risk-stratified screening.

The overall aim of the present research will be to establish whether providing women eligible for NHSBSP with personalised breast cancer risk (BC-Predict) estimation is feasible, by (a) measuring important potential harms and benefits of BC-Predict, (b) identifying the key drivers of the relative cost-effectiveness of embedding BC-Predict into the NHSBSP, and (c) attempting to understand the key issues affecting implementation of BC-Predict as part of the NHSBSP. This overall aim will be met by evaluating the BC-Predict system in a 16-month study running within the Greater Manchester, East Cheshire and East Lancashire NHS breast screening programmes, with the following three overarching objectives:

### Quantifying important potential benefits, particularly

Uptake of BC-Predict amongst women offered itUptake of risk consultation (for those eligible)Uptake of chemoprevention (for those offered it)Uptake of additional mammography (for those offered it)

### Quantifying important potential harms, particularly

Lower uptake of NHSBSP amongst women offered BC-PredictIncreased worry about breast cancerIncreased general state anxietyLess informed choices regarding screening uptake

### Quantifying indicative estimates of the NHS costs and patient consequences, including

Effects on health status and healthcare costsKey drivers of the relative cost-effectiveness of embedding BC-Predict into the NHSBSPExtent of uncertainty in the current evidence-basedThe potential value of future research.

## Methods/design

### Study design

A non-randomised fully counterbalanced study design will be used, to include equal numbers of participants from all sites who will be offered NHSBSP and BC-Predict. Specifically, in the initial 8-month time period, four screening sites will offer women eligible for breast screening BC-Predict. Three screening sites will offer women usual care NHSBSP. In the following 8-month time period the study sites switch to offer the other intervention (NHSBSP rather than BC-Predict; and vice versa). This ‘counter-balanced’ design will allow estimates of effect to be obtained from both within-sample and between-sample analyses.

### Setting

Women will be recruited from seven sites within three NHS Breast screening programmes: three sites within the Greater Manchester programme (Withington Community Hospital, Oldham lntegrated Care Centre and the Trafford mobile screening van only), and two sites each based in the East Cheshire (Macclesfield District General Hospital and Stockport mobile breast screening van locations) and East Lancashire (Burnley General Hospital and East Lancashire mobile breast screening van locations) programmes. Women invited to screening in East Cheshire and Withington/Trafford in the first 8 months of the study will be offered BC-Predict and women in East Lancashire and Oldham offered screening as usual. After 8 months, BC-Predict will be offered to women in East Lancashire and Oldham, with women in Cheshire and Withington/Trafford offered screening as usual.

### Participants

Recruitment is over a 16-month period and sites will each be open to recruitment to BC-Predict for a period of 8 months. Two groups of women will be invited to participate in the study (a) women invited for first time screening (“prevalent screens”), and (b) women invited during the screening round within which they reach 60 years (“incident screens” i.e. women aged 57 to 63 years). Posters advertising the study will be displayed in each of the participating screening sites to increase awareness of the study.

We will include women who are invited for usual care (NHSBSP) at each site to compare with women offered BC-Predict; however NHSBSP women will not be consented to the study as controls, as their personal information will not be accessed. Instead, core outcome measures will be obtained in aggregated form. This will provide a comparison with uptake to these services in the BC-Predict arm. Posters at study sites will inform women being offered NHSBSP that they can request their data is not included in any analysis.

Inclusion criteria are that the participant: (a) is born biologically female; (b) is invited for first breast screening appointment (any age); is aged 57 to 63 years (only at East Cheshire and East Lancashire NHSBSP); and (c) is able to provide informed consent and complete a risk assessment questionnaire. Exclusion criteria are that the participant: (a) is born male; (b) previously had breast cancer; (c) had bilateral mastectomy; or (d) has previously participated in the PROCAS study [10].

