#### Core outcomes

The following nine core outcomes will be compared at 6-months post completion of recruitment for those offered BC-Predict and those offered usual care (NHSBSP):

1. Screening attendance at first offered screening episode.

2. Screening attendance within 180 days of episode opening.

3. Number of technical recalls.

4. Number of recalls for assessment.

5. Number of routine recalls.

6. Number of breast cancer diagnoses (and type/grade).

7. Subsequent consultation in FHRP clinics (and mode: telephone or face-to-face).

8. Subsequent enrolment for more frequent screening.

9. Subsequent prescription of chemoprevention. Data will be collected on each of the following aspects of this: (a) participant agrees/disagrees in clinic to take chemoprevention, (b) chemoprevention not appropriate, (c) chemoprevention appropriate but prescription not filled, (d) chemoprevention appropriate and prescription filled.

Data for the nine core outcomes will be collected for each consented BC-Predict participant by the research staff for the 6 months following participants’ mammography appointment. For these participants, information will be available directly from NHSBSP and FHRP clinic records. For those in the usual care arm of the study, anonymised data will be provided by NHSBSP and FHRP services, to provide overall numbers for each of the core outcomes. We will prospectively record any refinements to procedures, to allow examination of how these impact on uptake of services.

We will also assess uptake of BC-Predict, and examine variation by study site. Where changes to recruitment procedures are made, we will keep notes of this, and examine the effects of these changes on uptake of BC-Predict, to inform how risk stratified screening should be rolled out. We will also examine variations in uptake of services by Index of Multiple Deprivation deciles derived from postcode of women [28] invited for NHSBSP, to assess any potential exacerbation of health inequalities brought about by BC-Predict.

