### Analysis plan and power calculations

#### Core outcomes

In total, approximately *n* = 18,700 women will be offered BC-Predict and *n* = 18,700 will be offered usual care NHSBSP over the total 16-month period. Based on the recruitment rate in PROCAS, *n* = 18,700 women being offered BC-Predict should result in 8000 women taking it up. The attendance rate to usual NHSBSP in Greater Manchester is 69% [5, 10].

Core outcomes will be compared for cohorts of women who are invited to BC-Predict and those who are invited to usual care (NHSBSP). Thus we will have in excess of 8000 participants in BC-Predict and NHSBSP groups for both comparisons: (a) within-site and (b) between sites over the same time period. The primary outcomes are binary. Logistic regression will be the primary statistical analysis method. We shall assess heterogeneity effects using interaction tests in the logistic regression, to examine differences in outcomes by time or location or screening type (prevalent v incident). Even in the presence of geographic or temporal heterogeneity of the effect, or of carryover effects continuing beyond the crossover period, we will still have sufficient data for a valid and fully powered comparison.

For core outcomes 1 and 2, we are interested in equivalence, in that we anticipate that invitation to BC-Predict will not substantially affect screening attendance. With 18,700 women in each group we will have in excess of 90% power to establish equivalence, defined as a 95%CI on the difference which does not exceed ±5% on the attendance rate at first offered appointment, if the latter is around 50% [37]. Similarly, we will have more than 90% power for the same comparison for eventual attendance within 180 days if the latter is around 70%.

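### The only opt-out notice described for usual-care women is a poster at the screening sites, seen mainly by attenders, which tends to lower the usual-care attendance rate in the equivalence comparison

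*Protocol article*

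**What the plan says.** The Participants section of the protocol article states that "NHSBSP women will not be consented to the study as controls, as their personal information will not be accessed". It continues: "Instead, core outcome measures will be obtained in aggregated form". The notice to these women is then described: "Posters at study sites will inform women being offered NHSBSP that they can request their data is not included in any analysis". No other notice to usual-care women is described.

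The Core outcomes part of Measures lists, as outcomes 1 and 2, "Screening attendance at first offered screening episode" and "Screening attendance within 180 days of episode opening". For usual care, "anonymised data will be provided by NHSBSP and FHRP services, to provide overall numbers for each of the core outcomes".

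The Analysis plan and power calculations section compares core outcomes between the cohorts invited to each arm. It treats outcomes 1 and 2 as equivalence questions, with equivalence defined as "a 95%CI on the difference which does not exceed ±5% on the attendance rate". The planning rates are about 50% at the first offered appointment and about 70% within 180 days, with 18,700 women per group. Lower screening uptake among women offered BC-Predict is one of the potential harms named in the objectives.

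Under Procedure, women offered BC-Predict are written to one or two working days after their screening invitation goes out, so they hear of the study whether or not they attend.

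**The concern.** The comparison is meant to cover everyone invited. A woman who never comes to a site is unlikely to see a poster there, so the chance of being excluded from usual care depends on the outcome being measured. Women who opt out leave both the numerator and the denominator. Because they are mostly attenders, the remaining usual-care cohort shows a lower attendance rate than the invited cohort really had.

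The direction matters. If BC-Predict reduced attendance, a usual-care rate that is too low would shrink the observed difference and make equivalence easier to declare. A larger sample does not remove a bias of this kind. Since usual-care data arrive as anonymised totals, the number of opt-outs may not be recoverable afterwards unless someone counts them as they occur.

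**Working it through.** **Inputs from the article.** 18,700 women per group; margin ±5 points; 95% CI; attendance about 50% at first appointment and about 70% within 180 days. Outcome 1 is read as first-appointment attendance, as the power paragraph reads it.

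**Assumptions.** The share *o* of eventual attenders who opt out is not in the documents; 1%, 5% and 10% are used to show a range. Women who never attend do not see the poster, all eventual attenders are equally likely to opt out, and women are treated as independent.

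**Step 1. The article's own power statement.** SE = √(2p(1−p)/18,700) and power = 2Φ(0.05/SE − 1.96) − 1.

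- p = 0.50: SE = 0.00517, half-width 1.96 × SE = 1.01 points, 0.05/SE − 1.96 = 7.7.
- p = 0.70: SE = 0.00474, half-width 0.93 points, 0.05/SE − 1.96 = 8.6.

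Power exceeds 99.99% in both cases, which agrees with the stated figure of more than 90%.

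**Step 2. Outcome 2 (70%).** Every opt-out is an attender, so the observed rate is 0.70(1−o)/(1−0.70o).

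- o = 1%: 0.693/0.993 = 69.8%, a fall of 0.2 points.
- o = 5%: 0.665/0.965 = 68.9%, a fall of 1.1 points.
- o = 10%: 0.630/0.930 = 67.7%, a fall of 2.3 points.

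**Step 3. Outcome 1 (50% at first appointment, 70% eventually).** The 20% of invited women who miss the first appointment but come later also see the poster, and they count as non-attenders here. The observed rate is 0.50(1−o)/(1−0.70o).

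- o = 1%: 0.495/0.993 = 49.85%, a fall of 0.15 points.
- o = 5%: 0.475/0.965 = 49.2%, a fall of 0.8 points.
- o = 10%: 0.450/0.930 = 48.4%, a fall of 1.6 points.

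**Step 4. Opt-out needed for a bias equal to the margin.**

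- Outcome 2: share of invited women removed = 0.05/(0.30 + 0.05) = 14.3%, that is 0.143/0.70 = 20% of attenders.
- Outcome 1: 0.50(1−o) = 0.45(1−0.70o) gives o = 0.05/0.185 = 27%.

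**Step 5. Effect on a wrong equivalence claim.** Suppose BC-Predict truly lowers 180-day attendance by exactly 5 points, to 65%. Without opt-outs the chance of declaring equivalence is 2.5%. With them it is about Φ((0.05 − observed difference)/SE − 1.96).

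- o = 1%: observed difference 4.79 points, SE 0.00485, chance about 6%.
- o = 5%: observed difference 3.91 points, SE 0.00490, chance about 60%.

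**The case against.** The strongest reply is that much of this rests on silence. The article says that posters will inform women; it does not say that posters are the sole notice, and the full protocol that might describe others is not shown. A reader might infer that the opt-out is offered *only* by poster. The text supports no more than that it is the only route described. This stands.

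A reader might also infer that *only attenders* can be removed. That is close to right for outcome 2, but wrong for outcome 1, where late attenders see the poster too. The bias there is still downward but smaller, as Step 3 shows. This also stands.

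Thirdly, a reader might infer that the BC-Predict cohort has no exclusions at all because its participants give individual consent. Consent covers only those who take up the offer, about 8,000 of 18,700. The article does not say how attendance is handled for BC-Predict invitees who do not consent, or whether they may object. The asymmetry between arms is therefore probable but not established.

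Fourthly, no opt-out rate is given, and nothing in the documents supports 5% or 10%. At 1% the bias is about 0.2 points or less, small against both the margin and the half-width of about 1 point. To say that the rule hides a fall in attendance would go too far.

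Finally, counts of opt-outs and sensitivity analyses are usual content of an analysis plan. That does not dispose of the point, because the article itself fixes both the notice and its consequence, exclusion from any analysis, while defining the comparison on all women invited.

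**Conclusion.** The point holds as a minor design weakness. As described, the opt-out acts mainly on women who attend, and so tends to lower the usual-care attendance rate on outcomes 1 and 2, in the direction that could partly mask a fall under BC-Predict.

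Its size depends on an opt-out rate that the documents do not give. With few opt-outs the equivalence conclusion is hardly touched. At about 5% the bias on outcome 2 (1.1 points) exceeds the CI half-width (0.93 points), and a true fall near the margin could well be missed. These figures rest on the planning rates of 50% and 70%, equal opt-out among eventual attenders, no opt-out by women who never attend, no equivalent loss in the BC-Predict cohort, and independence between women.

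**What to change.** Have each screening service log the number of opt-outs per site and period as a bare count, and report it.

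- **Outcome 2:** report a bounding analysis that adds the count back to the denominator and the numerator, as attended.
- **Outcome 1:** report two versions, one with all opt-outs counted as first-appointment attenders and one with them split in the observed ratio of first-appointment to later attenders. The first over-corrects. At 5% opt-out it gives 0.475 + 0.035 = 51.0% against a true 50%, so it is a bound and not an estimate. The split gives 0.475 + 0.035 × 5/7 = 50.0%, exact only if both kinds of attender opt out equally often.
- State whether equivalence holds across these bounds.

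Use only the aggregate count. The women were told that their data would be left out, so confirm beforehand that approvals and the poster wording allow the count to be used this way.

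The cost is one extra count per site and period, one sensitivity analysis, and that check of the approvals.
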